# Intervention development

1. **Theory-guided study development**

The stress and coping theory will be used to develop the intervention protocol.

**Appraisal step:** After finishing baseline assessments, the participant will be arranged to have an individual face-to-face meeting in a private room. The level of anxiety and depression at baseline will be considered. Besides, the intervener will interview the participants a question “How is your emotion recently?”. This will help the intervener know the level of anxiety and depression of the participant. After that, to identify the coping methods, the participants will be asked “what did you do to reduce your stress, recently?”. The intervener will advise participants to keep doing the positive coping methods and avoid the negative coping methods. Based on the result of the qualitative study in phase I, a list of music will be prepared. The questions “what is your favourite music?” “ what type of music that you do not like?” will be asked to participants. The list of patients’ music preferences will be noted to prepare for each participant. The conversation will be recorded and analysed to explain the result of the intervention effectiveness.

**Family support:** Family support is one of the most important coping methods that we identified in the qualitative study. Thus, in our program, the family member will be the person to support and encourage participants to self-practice MI and PMR at home. The family member is the person who lives with the patient and takes care of them every day. They will have an individual face to face meeting with the intervener. They will be informed of the psychological issues of the patients. The intervener will be introduced to the MCP program, its potential benefits. They will assign the task of motivating and monitoring the patient's daily practice.

**Coping strategy:** music listening combine with PMR

**Reappraisal:** Three weekly follow-up callings will be done by a research assistant. The content of the call will be to ask them about their emotion, any issues during practice, any day they cannot practice and the reason. The research assistant will answer questions and encourage them to keep practising. The call will be recorded and analysed.

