**Objectives**

To evaluate the potential screening, recruitment capability.

To identify potential adverse events associated with MCP.

To preliminary evaluate the effects of MCP on anxiety and depression and QoL.

To estimate the sample size for the future full-scale RCT.

To refine the study protocol for a future full-scale RCT.

1. **Sample size estimation**

Convenience sampling will be used to recruit the participants. The calculated sample size will follow the rules of thumb for finding an appropriate sample size in which the outcome is a continuous measurement. Julious (2005) recommended that for the evaluation feasibility of 2-group studies, a minimum of 12 participants of each group be considered

1. **Methods**

The study procedure, randomization, data collection, data analysis will be similar to the main study (see the main study below).

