The Intervention Group will receive the MCP training and their family’s member will have a meeting with the intervener. The patients will self-practice once every day. A “Self-practice Record Form (SRF)” will be given to participants to report the adherence, the adverse events, and the reasons for non-adherence. Once every week the research assistant 3 will individually call participants to encourage them to keep practising, remind fill SRF and asked their feelings, emotions. After three weeks of treatment, the participants will be required to fill DASS-21, FACT-G, SRF. After that, a three-week follow up will be carried out to test the persistence effect of MCP. After finishing the follow-up time, the participants will be asked to complete DASS-21, FACT-G, SRF by a research assistant.

The control group will receive standard care including health assessment, regular health advice and nutrition consultation during chemotherapy by doctors and nurses. To minimize the bias by contacting, weekly phone calls also will be carried out to participants. The content of the call will last around two minutes that will ask about their general health, medicine and remind them to return to the hospital next chemotherapy on time.

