**Mechanisms of impact**

adverse events (SPF)

Participant response to intervention (interview)

Outcomes

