**Fig. 3. MRC process evaluation framework (Moore et al., 2015)**

Contextual factors including family support, caring service in the hospital will be observed and documented by using field notes. The family support to practising the program at home, room to practice at home will be interview. Treatment will be documented. The experience of participants after training MCP the intervention will be interviewed and recorded. The intervention process will be recorded by comparing a checklist and an intervention manual. Participant’s adherence, adverse events will be recorded daily by a self-report form (SRF) and phone call follow-up. Participants’ responses will be collected by face-to- face individually interviewing after the intervention participants. Purposeful sampling with maximum variation strategy (Patton, 1990) with various characteristics and levels of adherence will be used. The interview will be recorded and analysed following qualitative content analysis of an interview text described by Graneheim and Lundman (Graneheim & Lundman, 2004).

1. **Ethics**

The study will be subjected to approval from The Joint Chinese University of Hong Kong - New Territories East Cluster Clinical Research Ethics Committee (The Joint CUHK-NTEC CREC) and the Ethics Committee in medical research, Nam Dinh University of Nursing, Vietnam, Vietnamese Ministry of Health.

This study will complies with the Declaration of Helsinki and follow the ethical principles for research that involved human subjects which are: autonomy, non-maleficence, and confidentiality (Beauchamp & Childress, 2001).

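### Adverse events are planned to be recorded through the MCP arm's practice form and calls, with no comparable recording planned in the control arm

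*Protocol*

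**What the plan says.** **Intervention arm.** In the Procedure section of the full-scale study, the paragraph on the Intervention Group introduces the SRF. Participants use it "to report the adherence, the adverse events, and the reasons for non-adherence". A research assistant will also, once a week, "individually call participants to encourage them to keep practising, remind fill SRF and asked their feelings, emotions". The Reappraisal step under Intervention development adds that these calls cover "any issues during practice, any day they cannot practice and the reason".

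**Process evaluation.** The text under Fig. 3 pairs adherence with safety and states that "adverse events will be recorded daily by a self-report form (SRF) and phone call follow-up". The figure itself names only the practice form as the source of adverse events.

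**Control arm.** The next paragraph of the Procedure section gives controls a weekly call of about two minutes "that will ask about their general health, medicine and remind them to return to the hospital next chemotherapy on time". The reason given for the call is to balance contact between the arms. No adverse-event question, form or record is mentioned.

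**Schedule and objectives.** Table 3 has no adverse-event row; only the SRF row, at Week 1-3, could carry such data. The one safety objective is in the pilot: "To identify potential adverse events associated with MCP". The pilot's Methods take over the procedure and data collection of the main study.

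**The concern.** All participants are receiving chemotherapy, and its side effects will be reported whichever arm a patient is in. A randomised control arm shows how often a symptom occurs without the intervention, but only if both arms are asked the same thing in the same way.

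Here one arm has a daily written form with an adverse-event item, plus calls about problems with practice. The other has a short weekly call with a general question about health. A non-specific symptom such as fatigue or dizziness on an MCP patient's form could come from the intervention or from chemotherapy, and the plan provides no matching control figure to help decide. What is at stake is the interpretation of the safety data, first in the pilot and then in the main trial.

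**Working it through.** **1. Which passages provide for adverse-event recording in each arm?**

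| Source in the protocol | MCP arm | Control arm |
|---|---|---|
| SRF (Procedure) | Yes, adverse events named | Not given; controls have nothing to practise |
| Weekly call (Procedure; Reappraisal) | SRF reminder, emotions, practice problems, missed days | General health, medicine, visit reminder |
| Process evaluation, text and Fig. 3 | SRF, plus follow-up calls in the text | No control route named |
| Table 3 | SRF row, Week 1-3 | No row |
| Reasons for dropout (Procedure) | Recorded | Recorded; not restricted to one arm |

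The process-evaluation sentence does not expressly limit its phone calls to the MCP arm. It names them alongside the SRF and in the same sentence as adherence, which points to the MCP calls. Even on the wider reading, the stated content of the control call has no adverse-event item.

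**2. What can be estimated as the plan stands?** A one-arm proportion, MCP only. For example, no events in 12 pilot patients leaves a one-sided 95% upper limit of 1 - 0.05^(1/12) = 0.22. A control rate collected on the same basis, and hence a risk difference, cannot be formed at any sample size.

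**3. What would equal collection give?** The protocol states no adverse-event figure, so there is none to reproduce. Inputs from the protocol are 42 per arm (Study sample) and a minimum of 12 per group (pilot, Sample size estimation). The background symptom rate p is not in the protocol; 10%, 30% and 50% are assumed, equal in both arms. The 95% half-width of the risk difference is 1.96 x sqrt(2p(1-p)/n).

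| p (assumed) | n = 42 per arm | n = 12 per arm |
|---|---|---|
| 10% | 1.96 x sqrt(0.18/42) = 0.128 | 1.96 x sqrt(0.18/12) = 0.240 |
| 30% | 1.96 x sqrt(0.42/42) = 0.196 | 1.96 x sqrt(0.42/12) = 0.367 |
| 50% | 1.96 x sqrt(0.50/42) = 0.214 | 1.96 x sqrt(0.50/12) = 0.400 |

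That is about 13 to 21 percentage points in the main trial and 24 to 40 in the pilot. At 40 evaluable per arm the main-trial values are nearly the same (about 13, 20 and 22 points). With that number, an excess would be detected with 80% power only if large: 10% against 36%, 30% against 61%, or 50% against 80%.

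**The case against.** The other side has several sound points.

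- **The safety aim is modest.** The full-scale objectives and hypotheses concern anxiety, depression, stress, quality of life and satisfaction. The pilot aims to identify potential events, not to estimate an excess over control. Reports from those who practise go some way towards that. A reader might infer that the pilot's objective cannot be met at all; the text does not support this.
- **Control events are not shut out.** They could surface through the general-health question or the recorded reasons for dropout. A reader might infer that the main trial would show a full count of MCP events against none in controls. That presumes an assumed background rate, complete capture on a form whose wording is not shown, and no control reports at all.
- **Some attribution is possible.** The daily form and the questions about practice problems let an event be linked in time to a session. It goes too far to say that MCP events can never be told from chemotherapy effects. The difficulty is confined to symptoms common to both arms.
- **No between-arm adverse-event comparison is planned.** The Data analysis section lists none, so bias in such a table is a risk only if someone makes one.
- **The stakes are limited.** The Ethics section treats both components as safe on the strength of earlier studies, and equal collection would still give wide intervals, above all in the pilot.

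All of this stands and limits the point. It does not remove it. A weekly open question and a daily prompted form do not give comparable counts, and no causality assessment is described to take the place of a control rate. Nor can this be left to the statistical analysis plan: whom to ask, how and how often is data collection, and answers never collected cannot be recovered in the analysis.

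**Conclusion.** The point holds as a gap in data collection. Adverse-event recording is planned through the MCP arm's form and calls, and control-arm ascertainment is neither planned nor comparable. Symptoms common in chemotherapy patients therefore cannot be set against a control rate, in a pilot whose stated aim is to find events associated with MCP. Events clearly linked to a practice session can still be identified individually.

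The efficacy conclusions are not affected: DASS-21 and FACT-G are collected at the same time points in both arms. The gain from closing the gap is a comparable, though imprecise, control rate. The half-widths of about 13 to 21 points (42 per arm) and 24 to 40 points (12 per arm) rest on assumed symptom rates of 10% to 50% and full follow-up. The finding itself needs no assumed rate; it follows from what the Procedure section, the process evaluation and Table 3 say.

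**What to change.** - Add one identically worded adverse-event question to the existing weekly call in both arms, at the same frequency. Word it without reference to practice, so that it means the same to a control patient.
- Apply this from the pilot onwards as well as in the main trial.
- Add a row to Table 3 for adverse events in both arms. At the same time, reconcile the SRF row, which shows Week 1-3 only, with the Procedure section, which also has the form completed after the follow-up period.
- Report the events from this question by arm, with confidence intervals and no claim of equivalence. Keep the daily SRF entries as descriptive data for the MCP arm only.

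**Cost.** If controls receive three calls each, as the MCP arm does, the question is added to 3 x 42 = 126 control calls in the main trial and at least 3 x 12 = 36 in the pilot. No visits, staff or patients are added. Control calls become slightly longer than the two minutes planned. Two limits remain: the between-arm estimates stay imprecise, and MCP patients, who are unblinded and keep a daily form, may still recall more when asked.

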**Hypothesis**

- The participants receiving MCP will have a significantly lower level of anxiety compared to the control group.
- The participants receiving MCP will have a significantly lower level of depression compared to the control group.
- The participants receiving MCP will have a significantly lower level of stress compared to the control group
- The participants receiving MCP will have significantly higher QoL scores compared to the control group.

1. **Study design**

A 2-arm, assessor-blinded randomised controlled will be conducted. Randomized Controlled Trial (RCT) is the best design to confirm an objective assessment of the true benefits of medical interventions (Doig & Simpson, 2005). The design will follow the Standard Protocol Items Recommendations for Interventional Trials (SPIRIT) (Chan et al., 2013) .

1. **Participants**

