Sequentially numbered, opaque, sealed envelopes will be prepared. To avoid tampering the creator of the envelope will sign on the back of the envelope (Clark et al., 2020). In addition, security measures will include inserting carbon paper into the envelopes to prevent trans-illumination (Clark et al., 2020). The person who creates and keeps the envelopes will be blinded and not be involved in recruiting participants to prevent the ordering of participants into groups (Efird, 2011). The envelopes that contain the names of the assigned group will be given to each patient after they sign the consent form. The envelopes will be opened only after the envelope has been irreversibly assigned to the participants (Doig & Simpson, 2005).

1. **Blinding**

It is impossible to blind participants or interveners because of the nature of the study (Huang et al., 2010). However, research assistants who assess outcome data, data entry and

analysis will be blinded to avoid the risk of assessor bias. The assistants will not participate in any other stage of implementing the program. The participants will be asked not to share their treatment allocation with the research assistants.

1. **Outcome measures and instruments**

Primary outcomes will include anxiety and depression, stress while the secondary outcome will encompass QoL.

Participants’ characteristic data will be collected via a self-designed demographic sheet which will include age, marital status, education level, employment, family income, stage of cancer, frequency of chemotherapy, treatment regimen.

Anxiety, depression and stress will be measured using the short form of the Depression Anxiety Stress Scale (DASS-21) (Lovibond & Lovibond, 1995). The instrument was translated and used in the Vietnamese population with good internal consistency (Cronbach’s alpha of depression subscale 0.72; Anxiety subscale 0.77; and Stress subscale 0.70, overall 0.88) (Tran et al., 2013). It includes 21 items rating scale, 7 items for anxiety (DASS21-A), 7 items for depression (DASS21-D) and 7 items for stress (DASS21-S). A 4-point Likert-type scale ranging from 0 to 3 was designed on each item, thus each subscale had a score from 0 to 21. The higher the score is the more severe is the anxiety, depression and stress.

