FACT-G will be used to assess QoL. It evaluates in functional scales on Social/family well-being (SWB); Emotional well-being (EWB) and Functional well-being (FWB). Each item is scored in one of five categories ‘Not at all’, ‘A little bit’, ‘some what’, ‘Quite a bit’ ‘Very much’. This tool has been translated and validated in Vietnamese by the FACIT system with the Cronbach’s alpha for the scale being 0.89.

1. **Procedure**

Patients receiving chemotherapy meeting research criteria will be identified by four research assistants who are nurses in the chemotherapy units. The research assistants will contact the participants to obtain written informed consent. If patients agree to participate in the study, they will be randomised to the intervention group or the control group. To assess the recruitment capability, the recruitment rate, the consent rate, and refusal rate, the reason for refusal, ineligibility, number of people signing the consent form will be recorded.

Participants will be assessed at 3-time points by an outcome assessor: after randomization, the baseline (T0) will evaluate the demographic form, DASS-21, FACT-G,.After finishing 3 weeks of self-practice intervention (T1) will assess DASS-21, FACT-G, ,after 3 weeks follow-up (T2) will assess DASS-21, FACT-G. After 6 weeks, the attrition rate will be calculated by recording the participants discontinue or loss of contact, and the reasons for drop out. Three weeks after baseline all the patients will return hospital for the next chemotherapy treatment. In the previous studies, timepoints assessed the effectiveness of MI PMR in cancer patients receiving chemotherapy based on the chemotherapy cycle. Yilmaz and Arslan (2015) evaluated PMR on breast cancer for three weeks (one chemotherapy cycle) and Chen et al. (2020) assess the consistency of MI after three weeks of follow-up. The data of T1 and T2 will be collected during hospitalization by the outcome assessor. The outcome assessor will be trained to collect data. The outcome assessor will be blinded to the study groups to collect data and not involve any steps of the study.

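### The Procedure section pairs the MCP-only practice record with the outcome forms at T1 and T2; if one person collects all three, assessor blinding is lost, and the text conflicts with Table 3

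*Protocol*

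**What the plan says.** Study design (full-scale study) states: "A 2-arm, assessor-blinded randomised controlled will be conducted". The Blinding section says that participants and interveners cannot be blinded. It confines blinding to "research assistants who assess outcome data, data entry and" analysis, adds "The assistants will not participate in any other stage of implementing the program", and asks participants not to disclose their allocation to these staff.

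The Procedure section gives T1 (week 3) and T2 (week 6) data collection to an outcome assessor and lists DASS-21 and FACT-G as what is assessed. Of this person it says: "The outcome assessor will be blinded to the study groups to collect data and not involve any steps of the study".

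Later in the same section, the paragraph on the intervention group introduces the SRF, on which patients record adherence, adverse events and reasons for not practising. For T1 it says: "After three weeks of treatment, the participants will be required to fill DASS-21, FACT-G, SRF". For T2 it says: "After finishing the follow-up time, the participants will be asked to complete DASS-21, FACT-G, SRF by a research assistant". The control-group paragraph describes standard care and short weekly calls and mentions no SRF.

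Table 3 marks DASS-21 and FACT-G at baseline, Week 3 and Week 6. It marks the SRF in the Week 1-3 column only.

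**The concern.** A record of daily MCP practice has no counterpart in the control arm, so anyone who handles it knows the patient's allocation. If it is completed at the same sitting as the primary outcome questionnaire, under the same person, the blinded collector is unblinded by the trial's own paperwork. The Blinding section treats disclosure by patients as a threat worth a specific instruction, yet the intervention paragraph asks those patients to complete a form that discloses it.

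Anxiety, depression and stress (DASS-21) and quality of life (FACT-G) are all collected at these two visits, so every primary outcome and the secondary outcome would be affected. Calling the trial assessor-blinded in reports would then be inaccurate.

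**Working it through.** No arithmetic bears on this point. The check sets the passages side by side.

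1. **Who holds the SRF?** It is described only in the intervention-group paragraph of Procedure. Its content (practice adherence and reasons for not practising) has no meaning for controls.

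2. **When is it completed?**

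| Place in protocol | SRF during weeks 1-3 | SRF at T1 (week 3) | SRF at T2 (week 6) |
|---|---|---|---|
| Procedure, assessment time points | not listed | not listed | not listed |
| Procedure, intervention group | yes, with weekly reminders | yes, with DASS-21 and FACT-G | yes, with DASS-21 and FACT-G |
| Table 3 | yes | no | no |
| Process evaluation | recorded daily, plus phone follow-up | no separate entry | no separate entry |

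   The intervention paragraph stands against Table 3 and against the assessor's task list.

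3. **Who collects at T1 and T2?** The time-points paragraph says the outcome assessor. The intervention paragraph names nobody for T1 and a research assistant for T2. If that assistant is the outcome assessor, the assessor handles the SRF. If not, the two paragraphs disagree about who collects T2 outcomes.

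4. **What follows if the intervention paragraph is applied and one person takes all three forms?** Each MCP patient assessed, at most the 42 allocated, is identified by the form. Each control can be identified by its absence. This applies at both post-baseline visits.

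5. **Are the staff roles separated?** The label research assistant covers several tasks:
   - the blinded assessors in the Blinding section;
   - the recruiting nurses ("Patients receiving chemotherapy meeting research criteria will be identified by four research assistants who are nurses in the chemotherapy units");
   - the weekly caller ("Once every week the research assistant 3 will individually call participants to encourage them to keep practising");
   - the person at T2.

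   The caller must know the arm, since the call encourages practice and reminds the patient to fill in the SRF. No passage gives two of these tasks to one person. Beyond numbering the caller, the protocol does not say which assistant does which task.

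**The case against.** The strongest reply is that the operational text already protects the blind. Table 3 keeps the SRF out of Weeks 3 and 6, the assessor's task list omits it, and the Process evaluation section treats it as a daily home record. On this view the intervention paragraph is loose drafting. It also says only that patients fill in or complete the forms, and never that they hand the SRF to the assessor. This stands in part: it shows a conflict within the document, not a settled loss of blinding. It does not remove the problem, because the intervention paragraph pairs the forms at both visits and site staff cannot tell which passage governs. The eligibility criteria add to the doubt by referring to six weeks of intervention, where Procedure describes three weeks of practice and three of follow-up. Those passages also need reconciling.

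A reader might infer that the same assistants recruit, coach by telephone and assess. The document does not show this. The Blinding section limits its statement to assistants who assess outcomes, enter data or analyse, Procedure names a separate outcome assessor, and the caller is identified by number. The bar on other work concerns implementing the program, which is most naturally the MCP intervention. Identifying patients and taking consent come before randomisation and do not in themselves reveal the arm. What remains is an ambiguous label.

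A reader might also take the neutral collector to be the design's only safeguard. It is not: data entry and analysis are blinded, patients are asked not to disclose, and controls receive weekly calls to balance contact.

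**Conclusion.** The point holds as an internal conflict with a conditional consequence. If the intervention-group paragraph is followed and one person collects all three forms, the collector is unblinded for both arms at T1 and T2 and the assessor-blinded description fails. If Table 3 and the assessor's task list are followed, the SRF does not break the blind. To say that blinding fails for the whole MCP arm as the protocol stands would go beyond the text.

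The size of any bias cannot be derived from the document. DASS-21 and FACT-G are reported by patients who know their arm, so an unblinded collector may add only modestly to a bias that is already possible. One could suppose a shift of 0.1 to 0.2 SD and set it against the planning effect of 0.74 (0.1/0.74 = 14%; 0.2/0.74 = 27%). Nothing in the protocol supports such a shift, and a mechanism such as politeness towards a known coach would require the collector to be the caller or intervener, which no passage says. Those percentages should not be used.

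The conclusion assumes that controls receive no SRF, as the control paragraph's silence and the form's purpose both indicate.

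**What to change.** Reconcile the intervention-group paragraph of Procedure with the assessment time-points paragraph and Table 3, so that all three agree on when the SRF is completed and returned.

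Remove the SRF from the outcome assessor's T1 and T2 task. Have it returned to the weekly caller, who already knows the arm, or to the intervener, separately and after DASS-21 and FACT-G are complete. The form should not simply be dropped, since it also carries adverse-event reports.

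State that the assistant who makes the weekly calls never collects T1 or T2 outcome data. In the same edit, name the T2 collector consistently as the outcome assessor, and identify by number which assistants recruit, call and assess.

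The cost is a few sentences and the reassignment of one form among existing staff. Sample size, visits and analysis are unchanged.
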